### Balance of treatment arms at baseline

Our baseline analyses will establish reference measures for follow-up analyses. We conducted bivariate assessments of balance between study arms at baseline (Table 1). As previously mentioned, 1589 households were enrolled into the study at baseline. Given we prioritized targeting of the primary female caregiver of the index child for baseline survey administration, a large majority (91%) of the respondents were female, by design. Of these 1589 respondents, 85% were the mother of the index child. Demographic variables were balanced across study arms, with no meaningful differences in the prevalence of key demographic variables between arms (Table 1). Similarly, key outcomes of interests were also balanced between the intervention and control arms at baseline. Importantly, facial cleanliness observations of the 1385 index children were similar to all other children aged 1–9 years in the study households (data not shown). This suggests that our index children serve as acceptable sentinels of behavioral outcomes for children of similar ages within the larger household.

At baseline, sanitation and hygiene conditions were found to be generally poor (Table 1). Only 40% of all households had a sanitation facility that was classified as improved based on the WHO/UNICEF Joint Monitoring Programme (JMP) for Water Supply and Sanitation definition. Further, 38% of respondents’ primary place of defecation during the 2 days prior to survey administration was in the open, and only 46% of respondents had defecated in any latrine during the two-day reporting period. These statistics, along with the fact that 39 of 50 *kebele* clusters randomly selected for inclusion in the *Andilaye* Trial have been triggered with CLTSH, and certified ODF, provide strong evidence that behavioral slippage is, indeed, an issue that needs to be addressed in Amhara and perhaps elsewhere in Ethiopia.

Our key health outcome, mental well-being, was shown to be poor, per the WHO-5 scale, amongst approximately one-third of respondents at baseline (Table 1). The baseline prevalence of anxiety, depression, and emotional distress amongst respondents was 29.7, 20.8, and 17.3%, respectively. The distributions of these scores were generally balanced, when comparing the intervention and control arms. Finally, the prevalence of diarrhea during the week (i.e., 7 days) preceding the survey was 9% among index children, and was also generally balanced across study arms (Table 1).

### Analytical methods

The primary method of analysis for all primary and secondary outcomes will follow an “intention-to-treat” analysis, which compares the intervention arm to the control arm, without regard to intervention fidelity or compliance. For binary outcomes, such as our targeted WASH behaviors, we will preferentially use log-linear binomial regression models. For continuous outcomes, such as the mental well-being scale scores, we will use linear regression models. All models will include an intervention variable as a fixed effect, and account for the stratified design through the inclusion of the *woreda* indicator variable [52], and incorporate generalized estimating equations with robust standard errors to account for the clustering of observations within *kebeles*.

The majority of our primary and secondary outcomes (shown in Additional file 5: Table S3) are binary variables, and for these we will preferentially use log-linear binomial models; however, log-linear binomial models are known to have difficulty converging, and so we may instead use modified Poisson regression if we encounter problems with convergence [53]. There is often interest in showing an absolute measure along with a relative measure (e.g., a prevalence ratio), so we will also present prevalence differences. We will use the same models as described above (e.g., log-linear binomial models), but use post-estimation commands to estimate the average marginal effects.

Given no imbalances were detected between study arms at baseline for any of the primary variables of interest (Table 1), we will not need to perform supplementary analyses, as outlined in our pre-analysis plan, to control for the baseline levels of these imbalanced variables in more fully adjusted models. For many of our outcomes, there is interest in determining the impact of the intervention across various sub-groups, such as sex, follow-up round (once multiple rounds of collection are completed), exposure to previous triggering, and modifiers such as water and sanitation insecurity. For select key outcomes, we will use interaction terms and/or stratification, and we will present the impact of the intervention at each level of the sub-group variable (e.g., separately for boys and girls).

Sub-optimal adherence, due perhaps to low uptake of interventions by participants or to poor implementation of the interventions, can lead to trial results that do not reflect the true efficacy of WASH. The intention-to treat analyses show a valid and unbiased causal effect for the effectiveness of a specific WASH program/intervention, but do not show the efficacy of WASH under ideal circumstances. If fidelity and adherence are heterogeneous, we will supplement our primary intention-to-treat analyses with an analysis that attempts to assess the impact of adherence to the *Andilaye* intervention on our primary outcomes of interest (e.g., an instrumental variable analysis, per-protocol analysis, or as-treated analysis). We have performed such analyses in other studies [54, 55].

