#### Intervention details

*Andilaye’s* intervention motto, “*Together we can be a strong, caring, healthy community*”, and related intervention components offer aspirational messages that emphasize the need for collective action to make positive change in the community and use verbal persuasion to enhance collective efficacy perceptions. The intervention focuses on three behavioral themes, informed by formative research: (1) sanitation, (2) personal hygiene, and (3) household environmental sanitation. Within these themes are 11 constituent practices targeted by the intervention; these practices were identified through formative research and the intervention design process as ones that could be targeted using demand-side approaches, and were seen as achievable, per stakeholder feedback (Additional file 1: Figure S1). We emphasize that behaviors usually represent a constellation of practices [38], and while the *Andilaye* intervention promotes 11 constituent practices of interest, these practices represent only three improved WASH behaviors. As such, our intervention actually focuses on fewer practices than many WASH interventions while also clearly specifying all necessary practices required to adopt the related improved behaviors.

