### Study outcomes and measures

Primary outcomes of interest include:Sustainability of WASH-related behaviors, as measured through the proportion of individuals and households consistently practicing improved targeted WASH behaviors, including: (1) sanitation, (2) personal hygiene, and (3) household environmental sanitation, more specifically, the 11 constituent practices identified above; andMental well-being, as measured through standardized mental well-being scale scores generated via the administration of the WHO-5 [40] and Hopkins Symptom Checklist (HSCL) [41].

Secondary outcomes of interest include:Short-term behavioral outcomes, measured as the proportion of households with improved (private or shared) latrines and washing facilities that are functional and available for use; proportion of households using functional latrines and washing facilities; proportion of households with all members exclusively using a latrine for defecation; proportion of households disposing of child feces in an improved latrine; proportion of households with all children in the household with a clean face and hands;Intermediate behavioral antecedents, measured as the proportion of households with improved knowledge regarding the implications of improved WASH practices (i.e., perceptions regarding negative externalities); proportion of households that indicate positive attitudes, perceptions toward improved sanitation and good hygiene practices; change in normative expectations related to open defecation, exclusive latrine use for defecation, and personal hygiene practices;Diarrhea period prevalence, as measured through caregiver self-report;Sanitation insecurity, as measured through changes in sanitation insecurity scale scores [19];Collective efficacy measures, as measured through changes in collective efficacy scale scores [42]; andWater insecurity, as measured through changes in water insecurity scale scores [43].

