### Sample size

We powered this study on mental well-being outcomes, as measure by the HSCL [41], which reflected the most restrictive primary outcomes in terms of required sample size. Various studies from Ethiopia and East Africa suggest that approximately 20–35% of rural women experience elevated symptoms of common mental disorders such as anxiety and depression [44, 45]. Drawing on two studies that have used the HSCL in East Africa [41], we estimated that average scores generated by this tool would be around 1.5 (SD 0.5). Using unpublished data from a large on-going study of young people in Ethiopia [46], we estimated the intra-cluster correlation (ICC) for a measure of mental health was approximately 0.05, although we suspected this may be low given the sample consists of young people, and the measure captures more severe mental health symptoms. Unpublished data from rural households in South Omo, Ethiopia are approximately 33% higher on a common mental health scale; suggesting that water insecurity is linked to mental health, and the effect is appreciable [47]. There are limited data on the impact of changes in WASH on mental well-being, so we used a similar difference to estimate our impact. Our sample size determination (Additional file 3: Table S2) indicated that we should recruit and enroll a total of 25 households from each of 50 study clusters (25 clusters per study arm). We increased our final sample size to accommodate for 20% of households being lost to follow-up. Our target sample, therefore, included 30 households in each *kebele* study cluster, or 1500 households in total (i.e., 750 per study arm).

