### Recruitment

From the *kebele* sampling frame, we employed a random number generator to identify 50 eligible *kebeles* clusters from across the three *woredas* targeted for our study. Given each of the three *woredas* vary with regard to their hydrogeological conditions and the size and number of *kebeles*, we used a stratified selection approach (at the *woreda* level). Of the 50 clusters, 22 were selected from Farta, 12 from Fogera, and 16 from Bahir Dar Zuria. Proportionally, these selected *kebeles* represented 51 (22/43), 38 (12/32), and 50 (16/32) percent of all *kebeles* in Farta, Fogera, and Bahir Dar Zuria, respectively. An even number of clusters were selected from each *woreda* to ensure an equivalent sample size between the intervention and control clusters selected from each *woreda*. Fogera had a slightly lower proportion of selected *kebeles* due to accessibility concerns given the frequency of floods in the low-land, marshy areas close to Lake Tana (Fig. 1). Our baseline results indicated that 78% (39 of 50) of *kebele* clusters randomly selected for inclusion in the *Andilaye* Trial have been triggered with CLTSH, and certified as ODF according to *Woreda* Health Office records. Another 14% (7 of 50) of study clusters have been triggered with CLTSH but have not yet been certified ODF, and the remaining 8% (4 of 50) have not been triggered with CLTSH, as of the commencement of this study, though they are slated for triggering.

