Recruitment took place within the home compounds during baseline data collection. Enumerators contacted adult members of the household; they explained the purpose of the visit, the purpose of the study, and asked the respondent if s/he would be willing to consent to participate in the study using a structured consent form (Additional file 4). Enumerators assessed household level eligibility by asking potential survey respondents a series of questions that lead to a determination of eligibility, and enrolled eligible and consenting households into the trial. During the consent process, enumerators informed respondents that they had the right to choose not to participate in the study, the right to refuse to answer any question, and the right to stop the survey for any reason at any point in time. Enumerators targeted primary survey respondents, based on the following order of priority: (1) the primary female caregiver of the index child, (2) any female household member who serves as a caregiver, (3) any male household member who serves as a caregiver, and (4) any household member over 18 year of age. If households were absent after three visits, no eligible adult respondent was available or refused to consent, or upon further conversation with the household, it became apparent that it was not eligible (e.g., no child aged 1–9 years), the enumerator recorded the information and notified the field supervisor prior to replacing that household with the next randomly selected household on the study roster. Of 1691 surveys initiated during baseline, 1589 (94%) households met all inclusion criteria and were enrolled into the study – 89 households more than the targeted sample size. Targeted households that did not meet inclusion criteria were excluded for the following reasons: 81 households did not have a household member between 1 and 9 years of age, 17 households had no eligible respondent available, three surveys were initiated but not fully completed, and one household did not consent to participate.

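### Name a small-sample correction and t reference for the kebele-clustered models, and give no separate effect for the 4 never-triggered kebeles

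*Protocol article*

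**What the plan says.** **Variance.** Analytical methods applies one specification to all models: an arm effect, woreda indicators, and a variance that will "incorporate generalized estimating equations with robust standard errors to account for the clustering of observations within" kebeles. It describes the link, a modified Poisson fallback and marginal effects. It names neither a finite-sample correction nor a reference distribution. A pre-analysis plan is mentioned but is not shown.

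**Sub-groups.** The listed sub-groups include "exposure to previous triggering, and modifiers such as water and sanitation insecurity". For select key outcomes these are to be examined by interaction terms, stratification or both, with the effect reported at each level.

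**Size of the triggering groups.** Recruitment gives 39 of 50 kebeles as triggered and ODF-certified and 7 as triggered but not certified, while "the remaining 8% (4 of 50) have not been triggered with CLTSH". Random allocation gives the ODF split as 20 intervention and 19 control. The arm split of the 4 never-triggered kebeles is not given.

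**Modifiers.** The Objective section names collective efficacy and water and sanitation insecurity as possible effect modifiers. Study outcomes and measures lists all three as secondary outcomes, for example "Collective efficacy measures, as measured through changes in collective efficacy scale scores". Intervention details says the intervention components "use verbal persuasion to enhance collective efficacy perceptions".

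**The concern.** The ordinary sandwich variance is biased downward when clusters are few, and a normal reference ignores the uncertainty in that variance. With 50 kebeles and 4 mean parameters, intervals for every primary and secondary outcome would be somewhat too narrow. In a sub-group of a handful of kebeles the same method can fail badly. A reader could then take a significant effect in never-triggered kebeles as evidence when it has little error control behind it.

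The second issue is which measurement round defines the modifiers. Grouping households by a follow-up value that the intervention may have changed compares groups formed after randomization, and contrasts between such groups are not clean intervention effects.

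**Working it through.** **Inputs from the article.** 50 kebeles, 25 per arm, in strata of 22, 12 and 16; 25 households per kebele required and 30 targeted (1589/50 = 31.8 enrolled); poor well-being 33.2%; ICC 0.026. Other ICCs used for the range are 0.005 to 0.077. Alpha is not stated, so 5% two-sided is assumed.

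**The article's own figure first.** It states power above 99% for a 12-point reduction.
- Design effect with 30 per kebele: 1 + 29 × 0.026 = 1.754.
- Effective n per arm: 750/1.754 = 427.6.
- SE = sqrt[(0.332 × 0.668 + 0.212 × 0.788)/427.6] = 0.0302, and 0.12/0.0302 is about 3.98.
- Power is about 97.7% two-sided and about 99.0% one-sided. The figure reproduces to within 2 points, so the inputs are sound for what follows.

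**False-positive rate if the variance is uncorrected.** With K kebeles and q mean parameters, an approximation is 2·P(t on K−q df > 1.96·sqrt((K−q)/K)).
- All 50 kebeles, q = 4 (intercept, arm, two woreda terms): 1.96 × sqrt(46/50) = 1.880, giving 6.65%.
- 11 non-certified kebeles (7 + 4; by arm 25−20 = 5 and 25−19 = 6), q = 2: 1.96 × sqrt(9/11) = 1.773, giving 11.0%.
- 4 never-triggered kebeles, q = 2: 1.96 × sqrt(2/4) = 1.386, giving 30.0%.

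**Simulation under no effect** (beta-binomial kebeles, 25 households each, 10,000 runs per setting, log and identity links; only the 50-kebele rows carry woreda terms):

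| Setting | Ordinary sandwich, normal reference | SE × sqrt(K/(K−q)), t on K−q df |
|---|---|---|
| 50 kebeles, ICC 0.005-0.077 | 6.2-7.3% | 4.6-5.6% |
| 46 triggered | 5.7-6.2% | 4.8-5.2% |
| 39 ODF-certified | 6.0-6.7% | 4.7-5.1% |
| 11 not certified (5 v 6) | 10-12% | 4.5-5.3% |
| 4 never triggered, 2:2 | 30-31% | 4.7-5.1% |
| 4 never triggered, 1:3 | about 51% | about 14% |

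An exchangeable GEE with 50 kebeles gave 6.4% (2,000 runs). A Kauermann-Carroll variance with a t reference (8,000 runs, 32 households per kebele) gave 5.3% for 50 kebeles, 5.4% for 11, and 5.4% for 4 split 2:2.

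**A pooled interaction model does not rescue the 4 kebeles if uncorrected** (6,000 runs). At 2:2 the never-triggered effect gives 28% and the interaction test 23%. At 1:3 these are 44-45% and about 38%. For the 11 non-certified kebeles they are 11-12% and 9-10%.

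**How likely is 2:2?** If 4 kebeles fall at random among 25 and 25, ignoring strata, 2:2 has probability 39%, 1:3 or 3:1 has 50%, and all four in one arm has 11%. In the last case no effect can be estimated within that level.

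**Modifier timing.** The Abstract (Methods) says the potential moderators are collected at baseline, midline and endline. Random allocation says kebeles were assigned after baseline. Baseline values therefore precede assignment and are safe to use. Analytical methods does not say which round is meant.

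**The case against.** The strongest reply is that this is a condensed article and the pre-analysis plan is not shown. Corrected sandwich estimators are robust standard errors too, so the wording does not exclude them. This stands: a reader might infer that the plan applies an uncorrected variance, but the text does not say so. The rates above are conditional on that choice, and for the main analysis the excess is only 1-2 points.

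A reader might also take 30% as the error rate of the previous-triggering analysis as a whole. It is not. It belongs to one possible level under an assumed 2:2 split, without woreda terms; the 46 triggered kebeles sit near 6-7%. The article does not define the levels. Because it reports arm balance by ODF status, a 39 v 11 grouping may already be intended. What survives is that the article promises an effect at each level without defining the levels, and one natural definition leaves 4 kebeles. Adding woreda terms does not help: with all three woredas present, 4 kebeles would support 4 parameters and leave no degrees of freedom.

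The simulated outcome is binary, whereas the article analyses the well-being scale scores by linear regression. That is fair, but the approximation depends on the number of kebeles and parameters, not on the outcome being binary.

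Finally, a reader might infer that the modifiers named in Analytical methods are themselves intervention targets, or that follow-up values will be used. Explicit targeting is documented only for collective efficacy; water insecurity is a secondary outcome outside the three behavioral themes. No section says follow-up values will define the groups, and measuring a construct at baseline as a modifier and its change as an outcome is no contradiction.

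**Conclusion.** The point holds in conditional form. With the ordinary sandwich and a normal reference, the main analyses would run at about 6-7% instead of 5%. That is a small excess, but it touches every outcome and is easily avoided. The more serious exposure is a separate result for never-triggered kebeles: about 30% false positives at the favourable 2:2 split, about 51% at 1:3, and still about 14% at 1:3 after simple scaling. No reported test in that level can be relied on unless the arm split is known and favourable. These figures assume a 5% two-sided level, the stated prevalence and ICCs, and, for the 4 kebeles, that never-triggered status forms a level of its own. The modifier issue is a request for clarification and becomes a fault only if follow-up values are used.

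**What to change.** 1. For all GEE models, specify a small-sample corrected sandwich variance (Kauermann-Carroll or Fay-Graubard) with a t reference on kebeles minus parameters.
2. Define the triggering sub-group as ODF-certified (39) against not certified (11; 5 v 6 by arm), tested by an interaction in the full model with the same correction. The corrected rates above for the 11 kebeles come from analysing them alone, and the interaction draws its precision mainly from those 11. A t reference that counts all 50 kebeles may be slightly generous, which is worth noting when the result is reported.
3. Give no stand-alone test or interval for the 4 never-triggered kebeles; describe them only.
4. State that water insecurity, sanitation insecurity and collective efficacy act as modifiers through their baseline values.

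**Cost.** A software option and a few sentences. Primary intervals widen by 2.013/1.960 × sqrt(50/46) = 1.07, about 7%, relative to the uncorrected ones. Most of that removes false precision. The planning cost comes from the t quantile alone: (2.013 + 0.842)/(1.960 + 0.842) = 1.02, which moves the two-sided detectable difference at 80% power from about 8.7 to about 8.9 points with 30 households per kebele. The article states 8 points. The 8.7 is a two-sided recalculation, and a one-sided 5% level gives about 7.7, so that gap is separate from this point.

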## Discussion

This study will evaluate the impact of *Andilaye*, a demand-side sanitation and hygiene intervention, on sustained adoption of improved sanitation, personal hygiene, and household environmental sanitation behaviors and mental well-being above and beyond current CLTSH interventions. As outlined below, there are several documented limitations of CLTSH in Ethiopia, and WASH programming more broadly, that the *Andilaye* intervention was designed to address.CLTSH, the key approach to improving sanitation coverage and utilization in Ethiopia, has facilitated considerable changes in coverage of basic sanitation. However, some of these gains have not been sustained, and incremental improvements to improve sanitation (i.e., progress up the sanitation ladder) have not been widely promoted or achieved [29].WASH programs, more broadly, have focused on catalyzing initial behavior change, and have placed little, if any emphasis on the habituation of improved behaviors and behavioral maintenance. Such approaches have fostered behavioral slippage, or regression back to unimproved behaviors and practices, and poor sustainability of behavioral outcomes and potential health impacts [56].CLTSH largely focuses on leveraging shame to change norms around open defecation, but these negative affective motivators may not be the most appropriate or effective drivers of change, and may actually erode mental well-being. As indicated by our formative research, focus on negative affective motivators, poor facilitation of initial triggering, and a lack of post-triggering follow-up has left many communities with negative impressions of CLTSH initiatives.Behaviors and facilities promoted by existing programs are aspirational but require considerable effort and/or capital investment to achieve. A focus on small, incremental improvements in WASH practices and facilities may be viewed as more achievable by program participants, particularly in low resource settings, and as such, may garner greater success.HEWs charged with implementing CLTSH have many responsibilities, few tools, and little capacity to continually reinforce messages [57]. Although Cluster Health Centers are expected to closely support and monitor HEWs, due to a number of reasons, there is limited support extended to them.Siloed approaches within the health and development sectors, namely WASH and those vertical programs involved in the control and elimination of NTDs, prevent the integration and harmonization of NTD and WASH behavior change initiatives [58]. For instance, FMoH’s current CLTSH programming focuses on handwashing with soap at key times, yet overlooks the opportunity of promoting routine facewashing despite the high prevalence of trachoma in the country.While the focus on diarrheal disease prevention and growth faltering have driven investments in WASH, recent evidence suggests that, in sub-Saharan Africa, basic improvements may not be enough to impact these health outcomes [49, 59]. However, factors contributing to the influence of water, sanitation, and hygiene on other important health outcomes, such as mental well-being, remain under-studied.

The *Andilaye* intervention reflects a potential alternative to CLSTH, and evidence generated by the *Andilaye* Trial may serve to address several knowledge gaps related to integrated and holistic community-based, demand-side sanitation and hygiene programming in Ethiopia and beyond. Few community-based WASH interventions have incorporated specific strategies to enhance behavioral maintenance capacity, and limited evidence exists regarding the influence of various inter-personal factors on sustained behavioral change. Evidence generated by this CRT may also indicate how (i.e., through which mechanisms) interventions can bring about sustained improvements in sanitation, hygiene, and less studied health outcomes, such as mental well-being.

Limitations of this CRT include reliance on local government partners to implement and supervise the implementation of the *Andilaye* intervention. Our mixed methods process evaluation will allow us to assess intervention fidelity and adherence, and document any potential bottle-necks that may threaten the intended roll-out of intervention activities. Evidence from the process evaluation will help us interpret the results from the *Andilaye* Trial. Policy-relevant findings and related recommendations regarding the feasibility and effectiveness of the *Andilaye* intervention will be shared broadly when endline data have been collected and analyzed.

